### Sample size calculation

#### Primary outcome

Based on our previous published data, the rate of tibial cartilage volume loss in the control group was 3.0 +/− 3.0 per annum [47]. A 33 % reduction (that is, 1 %) in this rate is clinically significant since this indicates a significant reduction in structural progression of cartilage damage. Our previous work has shown that a 1 % reduction in the annual rate of cartilage volume loss over 2 years decreased the need for knee replacement surgery by 20 % over a 3-year period based on the strong association between the rate of cartilage volume loss and subsequent knee replacement [48]. With 140 participants in each arm, we will have 80 % power to detect a 30 % reduction in the rate of cartilage volume loss in the intervention group (2.0 %) compared with the control group (3.0 %), with alpha error 0.05, two-sided significance. Given our previous experience in such studies, we expect a maximum dropout rate of 20 % over 2 years. Therefore, a total of 350 participants (175 in each arm of the study) will be recruited.

#### Secondary outcome

Based on our reported progression rate of 68 % for cartilage defects [49] and 21 % [14] for BMLs over 2 years, with 140 participants per arm we will have 80 % power to detect a 17 % difference in the progression of cartilage defects and a 12 % difference in the progression of BMLs between the intervention group and the control group. With 140 in each arm, we will be able to detect a 30 % reduction in the WOMAC pain subscale in the intervention group.

### Statistical analysis

The primary analyses will be intention-to-treat analyses of primary and secondary outcomes. Per protocol analyses (according to protocol adherence for patients who have taken all the study medication and have had all the outcome measures) will be performed as the secondary analyses. Intention-to-treat analysis will be carried out by using multiple imputation [50], provided that patients have had a baseline MRI. This analysis only requires missing data to be missing at random to be valid. Differences within a treatment group between follow-up and baseline measures will be assessed using a paired samples *t*-test. The clinical efficacy measures, that is, changes in pain and function, will also be analysed using the normalised area under the curve for difference in scores from baseline to month 24. Differences between treatment groups will be assessed using independent samples *t*-tests, ANCOVA (for continuous variables) or chi-squared tests (for dichotomous variables). Multiple linear regression for continuous endpoints or logistic regression for binary endpoints could be carried out as supplementary analyses for additional adjustment for imbalanced baseline factors. Analyses of treatment efficacy will be done by censoring participants at the time of any protocol deviation and developing a model for the probability of deviation, followed by weighted analyses using only the uncensored participants where the weights are the inverse probability of censoring. This produces estimates of treatment effect as if there were full compliance with the protocol in this trial and is far preferable to per protocol analyses based on (unweighted) observed compliance [51]. Pre-specified analyses to identify subgroups which may respond better to treatment will be examined using stratified analyses; variables include radiographic OA and co-pathology present on MRI.

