**Methods/design:**

350 patients with symptomatic knee OA will be recruited through the OA Clinical Trial Network (in Melbourne, Hobart and Adelaide). They will be randomly allocated to the two arms of the study, receiving either 40 mg of atorvastatin or identical placebo once daily for 2 years. Magnetic resonance imaging of the knee will be performed at baseline and 2 years later. Knee structure, symptoms and function will be assessed using validated methods. The primary outcome is annual percentage change in knee cartilage volume. Secondary outcomes include progression of cartilage defects, bone marrow lesions, knee pain and function. The primary analysis will be by intention to treat, but per protocol analyses will also be performed.

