### Study procedure

At screening, participants will complete questionnaires, have a knee X-ray, and undergo biochemical testing including liver function tests, creatine kinase and renal function tests, to ensure inclusion criteria are met. The study knee will be defined as the one with symptomatic OA; if both are symptomatic, the one with least severe radiographic OA (joint space narrowing) will be studied, to reduce loss to follow-up for joint replacement. After screening, study visits will be scheduled for 0 (baseline), 6, 12 and 24 months (Table 2). The same researchers, who are blinded to treatment allocation, will measure all clinical variables, administer questionnaires, monitor compliance, and record adverse events at these visits. Compliance by trial medication will be assessed by pill count. Biochemical testing will be performed at 4 weeks, and at 6, 12 and 24 months. At baseline and 24 months the index knee will be imaged on the same whole-body MRI unit.

**Table 2 Tab2:** Timetable and measures to be made

	Screening	Month 0 (baseline)	Week 4	Month 6	Month 12	Month 18	Month 24
X-ray	√						
Biochemical testing	√		√	√	√		√
Questionnaires	√	√		√	√		√
Knee VAS	√	√		√	√		√
Knee WOMAC		√		√	√		√
IPAQ		√					√
SF-36		√					√
Concomitant medications	√	√		√	√		√
Smoking		√					√
History of joint disease	√	√					√
Co-morbidities	√	√					√
Education and occupation		√					
Physical examination		√					√
Height and weight		√					√
Lower limb muscle strength		√			√		√
Knee MRI		√					√
Compliance and adverse events				√	√	√	√
Medication dispensing		√		√	√	√	

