### Withdrawal

If participants withdraw from the study before 2 years of follow-up, the reason and date will be recorded. If the participant withdraws after a minimum of 6 months of treatment, he/she will be requested to have a second knee MRI scan and complete the questionnaires.

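### The adherence analyses allow no missed tablet, missing measure or deviation; read literally, the per-protocol set would fall well below the planned 140 per arm

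*Protocol article*

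**What the plan says.** All of this is in the protocol article.

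- **Treatment (Abstract, Methods/design):** participants are allocated to "receiving either 40 mg of atorvastatin or identical placebo once daily for 2 years".
- **Adherence measurement (Study procedure):** "Compliance by trial medication will be assessed by pill count". No threshold or expected adherence is given.
- **Per-protocol set (Statistical analysis):** the secondary analysis is "for patients who have taken all the study medication and have had all the outcome measures".
- **Weighted efficacy analysis (same section):** it works by "censoring participants at the time of any protocol deviation and developing a model for the probability of deviation". After that, the estimate is computed in people who were never censored, with inverse-probability weights. The claim made for it is: "This produces estimates of treatment effect as if there were full compliance with the protocol in this trial". The term deviation is neither defined nor graded.
- **Timing of the MRI outcome (Study procedure):** "At baseline and 24 months the index knee will be imaged on the same whole-body MRI unit". Under Withdrawal, someone who leaves after at least 6 months of treatment is the exception: "he/she will be requested to have a second knee MRI scan and complete the questionnaires".
- **Primary analysis (Statistical analysis):** intention to treat, with multiple imputation.

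**The concern.** The article does not leave these rules open. It states them, and with universal wording: all the medication, all the measures, any deviation. A later analysis plan with an ordinary adherence threshold would contradict the published rule rather than complete it.

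Followed literally, the per-protocol set keeps only people with a perfect record over two years of daily dosing. It also ties each outcome to every other: Table 2 schedules WOMAC at months 0, 6, 12 and 24, so a missed month-6 questionnaire would exclude someone whose two MRI scans are complete. In the weighted analysis, a participant censored before month 24 has no scheduled on-protocol scan for the primary outcome.

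At stake is whether the adherence analyses can tell the reader anything. If kept as written, they may be small and highly selected. If the rule is loosened later, the choice should not be open to influence from the results.

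**Working it through.** **1. The plan's own sample size.** Inputs from Sample size calculation: difference 1.0 percentage point per annum (3.0 v 2.0), SD 3.0, two-sided alpha 0.05, power 80%, dropout 20%.

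- n per arm = 2 × (1.960 + 0.842)² × 3² / 1² ≈ 141.3, so 142. The plan has 140.
- Power with n per arm = Φ(1 / (3 × √(2/n)) − 1.960). At n = 140 this is Φ(2.789 − 1.960) = 79.6%.
- 140 / 0.8 = 175 per arm, 350 in total.

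The plan's figures reproduce, so 140 per arm is a fair reference.

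**2. Number of doses.** Once daily for 2 years: 2 × 365 = 730.

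**3. Share taking every dose, common independent adherence p (assumed).** Share = p^730.

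| p | Share taking all 730 | Of 140 per arm |
|---|---|---|
| 99% | 0.07% | 0.1 |
| 99.5% | 2.6% | 3.6 |
| 99.9% | 48% | 67 |

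At 99.9% the average participant misses 730 × 0.001 = 0.73 tablets in two years. Adherence still closer to perfect keeps more: 99.95% (0.365 missed tablets on average) leaves 69%, or 97 of 140. Half is therefore the top of the range used here, not a mathematical ceiling.

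**4. Share taking every dose, adherence varying between people (assumed).** Beta-binomial with mean m and precision s: share = B(ms + 730, (1 − m)s) / B(ms, (1 − m)s). A smaller s means that missed doses are more concentrated in some people.

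| Mean adherence | s = 10 | s = 5 | s = 2 |
|---|---|---|---|
| 90% | 1.2% | 7.6% | 29% |
| 95% | 11% | 28% | 54% |

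For comparison only, a threshold of 80% of tablets would keep 83% to 96% of participants in these six scenarios.

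**5. Power for the planned difference in the reduced set.** Same power formula as in step 1.

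| Share of 140 kept | n per arm | Power |
|---|---|---|
| 5% | 7 | 9% |
| 10% | 14 | 14% |
| 20% | 28 | 24% |
| 30% | 42 | 33% |
| 50% | 70 | 50% |

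These figures count only missed tablets. The requirement for all outcome measures reduces the set further, by an amount the article gives no means to estimate.

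**6. Weighted analysis.** Weighting can correct selection on modelled factors, but it does not bring back lost information. Effective n = n / (1 + CV²), where CV is the coefficient of variation of the weights. As an illustration, with 20% kept and CV = 1 (both assumed), 28 / 2 = 14 per arm, and power is 14%.

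**7. Timing.** The scan requested on withdrawal could supply an annualised change, because the primary outcome divides by the time between scans. But under a rule that censors when the deviation occurs, that scan comes at or after the censoring time. WOMAC at months 6 and 12 can still contribute for people censored later, so the symptom outcomes are less affected than the MRI outcome.

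**The case against.** A reader might infer that both analyses would rest on almost nobody, or that the weighted analysis would use the same tiny set with extreme weights. The article does not support either.

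- **No adherence figure is given.** Near-empty sets follow from independent misses at 99.5% per-dose adherence or less. When adherence varies between people, the share kept ranges from about 1% to 54%, so clustering changes the picture materially.
- **The two sets are defined differently.** The per-protocol set needs all tablets and all measures. The weighted analysis needs no protocol deviation, and that term is undefined. The stated aim of full compliance favours the strict reading, but if only major deviations were meant, the set could be large. The weights cannot be derived from the article.
- **Not every outcome waits for month 24.** WOMAC is collected earlier, and an MRI is requested on withdrawal after 6 months.
- **Thresholds, deviation lists and weight handling usually belong in a full protocol or analysis plan.** Their absence from an article is not an error. The article also cites a methods source for the weighting, and itself prefers weighting to an unweighted per-protocol analysis.
- **The primary analysis is intention to treat.** The main conclusion, the sample size and error control do not depend on these sets.

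The first three points limit the size of the problem, and the last limits its importance. The fourth does not remove it, because the article states absolute rules rather than staying silent. The same applies to the full-compliance claim: it is made without conditions, while the same section does state the missing-at-random condition for multiple imputation.

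**Conclusion.** The point holds as a defect of wording in the secondary adherence analyses. Read literally, the per-protocol set would be well below 140 per arm: from near 0 to about half, depending on assumed adherence. Power for the 1-point difference would be about 10% or less at the low end and about 50% when half remain. These figures rest on 730 doses, the plan's SD of 3.0, and adherence patterns that the article neither gives nor excludes.

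For the weighted analysis the loss cannot be sized until a deviation is defined. What can be said is that, for the MRI outcome, anyone censored before month 24 has no scheduled on-protocol scan, and that the full-compliance claim is stated more strongly than the method allows. The primary intention-to-treat analysis is untouched. The change is worth making, but the trial's main result does not depend on it.

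**What to change.** Before unblinding, and in writing:

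1. Replace the requirement of all study medication with a pre-specified pill-count threshold, for example at least 80% of tablets. The figure is for the sponsor to choose.
2. Require only the outcome under analysis to be observed, not every outcome measure.
3. Replace any protocol deviation, as the censoring event, with a named list of important deviations.
4. Report the numbers retained per arm and the distribution of the weights.
5. Say that the full-compliance interpretation holds only if there are no unmeasured common causes of deviation and outcome.

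The cost is wording only: no extra participants, visits or measurements. The downside is that the per-protocol estimate then averages over slightly imperfect adherence.

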### Randomisation and blinding

Allocation of participants in a 1:1 ratio to either the intervention or control group will be based on computer-generated random numbers prepared by a statistician with no involvement in the trial. Block randomisation will be performed using a central automated allocation procedure, stratified according to the study site. The randomised controlled trial will be a double-blind one, with both participants and investigators assessing outcomes blinded to treatment allocation. Allocation concealment and double blinding will be ensured by 1) the medications being dispensed by the hospital clinical trial pharmacy in each site; 2) the use of an identical placebo tablet; 3) objective measures of knee structural changes being made by trained observers blinded to group allocation and the time sequence of MRI scans; 4) subjective measures being taken by research assistants blinded to group allocation.

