### Outcome measures

#### Knee MRI

Knee MRI acquisition at the three study sites is presented in Table 3, including details of sequences and parameters being used.

**Table 3 Tab3:** Magnetic resonance imaging sequences and parameters at three study sites

	Machine and coil	T1 sagittal	Proton density sagittal
Melbourne	3.0 T whole body MR unit (Achieva, Philips Medical Systems), using a commercial 16-channel transmit-receive knee coil	T1-weighted fat suppressed 3D gradient recall acquisition in the steady state; flip angle 15 degrees; repetition time 25.9 msec; echo time 9.2 msec; field of view 16 cm; 320 × 320 matrix; one acquisition; partition thickness 0.5 mm	Proton density fat-saturated acquisition; flip angle 90 degrees; repetition time 3,817 msec; echo time 25 msec; field of view 16 cm; 720 × 720 matrix; slice thickness 2.5 mm
Hobart	1.5 T whole-body MR unit (GE-Signa; GE Healthcare, Buckinghamshire, UK) using a dedicated 8-channel knee coil	T1-weighted fat-saturated 3D gradient-recalled acquisition; flip angle 30 degrees; repetition time 31 msec; echo time 6.8 msec; field of view 16 cm; 512 × 512 matrix; one excitation; slice thickness 1.5 mm	Proton density fat-saturated 2D fast spin echo sequence; flip angle 150 degrees; repetition time 3,800 msec; echo time 39 msec; field of view 16 cm; 512 × 512 matrix; 3 excitations; slice thickness 3 mm
Adelaide	1.5 T whole-body MR unit (Aera, Siemens) using a dedicated 15-channel transmit-receive knee coil	T1-weighted fat-saturated 3D gradient-recalled acquisition; flip angle 30 degrees, repetition time 14.7 msec; echo time 6.74 msec; field of view 16 cm; 448 × 448 matrix; one excitation; slice thickness 1.5 mm	Proton density fat-saturated 2D fast spin echo sequence; flip angle 180 degrees; repetition time 3,200 msec; echo time 39 msec; field of view 16 cm; 320 × 320 matrix; 1 excitation; slice thickness 3 mm

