#### Concomitant medication use

Concomitant medication use including glucosamine, chondroitin, corticosteroids and non-steroidal anti-inflammatory drugs will be allowed during the trial but will be documented. There is no definitive data showing that these treatments affect cartilage loss. The randomisation process is the most effective method for ensuring that two groups are as similar as possible with respect to known confounders and unknown potential confounders including treatments. We will adjust for medication use in the analyses.

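### Site, the stratification factor, is in no stated between-arm analysis; the primary test and its covariates are left open, and adjustments promised elsewhere are in no model

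*Protocol article*

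**What the plan says.** All references are to the Protocol article.

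- **Randomisation and blinding:** "Block randomisation will be performed using a central automated allocation procedure, stratified according to the study site". Allocation is 1:1.
- **Statistical analysis, main comparison:** the arms are compared by two-sample t-tests, "ANCOVA (for continuous variables) or chi-squared tests (for dichotomous variables". No covariate is named, neither continuous method is assigned to the primary outcome, and site is not mentioned.
- **Statistical analysis, further adjustment:** linear or logistic regression "could be carried out as supplementary analyses for additional adjustment for imbalanced baseline factors".
- **Concomitant medication use:** "We will adjust for medication use in the analyses". The section on cigarette smoking history makes the same promise for smoking status, and the section on tibial plateau bone area says cartilage volume will be corrected for that area. None of the three reappears in Statistical analysis. Table 2 schedules medication at screening and at months 0, 6, 12 and 24, and smoking at months 0 and 24.
- **Knee MRI, Table 3:** Melbourne scans at 3.0 T with 0.5 mm partitions; Hobart and Adelaide scan at 1.5 T with 1.5 mm slices.
- **Sample size calculation:** 140 per arm after dropout, for 3.0 % against 2.0 % annual loss, SD 3.0, two-sided alpha 0.05 and 80 % power. No covariate enters.

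**The concern.** Stratifying by site balances the arms within site. If site predicts the outcome, the estimated difference is then less variable than an unadjusted standard error claims, and an analysis without site gives that precision away. Leaving baseline out of a change-score comparison loses precision in the same manner.

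The second issue is that the analysis is not pinned down. From Statistical analysis alone, the primary result could be a t-test or an ANCOVA on any covariate. From the sections on medication, smoking and bone area, it could be adjusted for those as well. A trigger based on observed imbalance picks covariates from the data rather than by prognostic strength, although the plan itself names knee angle and meniscal lesions as influences on cartilage change. Medication use carries a further risk: values recorded after randomisation may respond to treatment, and adjusting for them can bias the treatment effect.

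**Working it through.** **1. Reproduce the design.** Difference 1.0 point per year, SD 3.0, two-sided alpha 0.05.

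- n per arm = 2 × (1.960 + 0.842)² × 3.0² / 1.0² = 141.3, so 142 against 140 stated.
- Power at 140: SE = 3.0 × √(2/140) = 0.3586; 1.0/0.3586 − 1.960 = 0.829; power 79.6 % (79.4 % with the t distribution).
- Dropout: 140/0.80 = 175 per arm, 350 in total.

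The stated figures reproduce with an unadjusted comparison, so planned power does not depend on covariates.

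**2. Gain from adjusting the primary outcome.** The documents give no R², the share of outcome variance explained by site and baseline, so a range is assumed. The residual SD becomes 3.0 × √(1 − R²).

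| Assumed R² | Power at 140 per arm | n per arm for 80 % |
|---|---|---|
| 0 | 79.6 % | 142 |
| 0.02 | 80.4 % | 139 |
| 0.05 | 81.6 % | 135 |
| 0.10 | 83.6 % | 128 |
| 0.20 | 87.7 % | 114 |

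With the t distribution, R² of 0.05 and 0.10 give 81.4 % and 83.4 %.

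**3. Effect of omitting site alone.** Simulation with 20,000 runs per setting, arms balanced within three sites (47, 47 and 46 per arm), total SD held at 3.0:

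| Assumed site share of variance | Type I error, t-test / site-adjusted | Power, t-test / site-adjusted |
|---|---|---|
| 2 % | 0.047 / 0.049 | 79.8 % / 80.4 % |
| 5 % | 0.045 / 0.052 | 80.1 % / 81.6 % |
| 10 % | 0.040 / 0.051 | 80.6 % / 83.3 % |
| 20 % | 0.030 / 0.051 | 82.0 % / 87.3 % |

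The t-test errs on the conservative side. Power forgone is about 0.6, 1.5, 2.7 and 5.3 points. These gaps are smaller than a comparison with 79.6 % suggests, because stratified allocation already gives the t-test a little extra power.

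**4. WOMAC change.** With equal SDs σ at baseline and follow-up and correlation ρ, the change score has variance 2σ²(1 − ρ) and ANCOVA on baseline has σ²(1 − ρ²). The SE ratio is √[2(1 − ρ)/(1 − ρ²)] = √[2/(1 + ρ)]. The documents give no ρ. Assumed values of 0.4, 0.5, 0.6 and 0.7 give 1.20, 1.15, 1.12 and 1.08.

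**5. Sections side by side.** Statistical analysis makes regression adjustment optional and supplementary. The medication and smoking sections state adjustment without qualification. The bone-area sentence concerns cartilage volume and does not say whether it applies to percentage change. These statements cannot all describe one primary analysis.

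**The case against.** The strongest reply is that model detail belongs in an analysis plan, which is not shown, and that an article condenses. For an exact covariate list this stands. It does not answer the whole point: the article affirmatively lists unadjusted tests, makes regression supplementary, sets an imbalance trigger, and promises adjustments elsewhere that its statistics section does not carry. An analysis plan would have to depart from one section or another.

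A reader might infer several stronger claims that the documents do not support:

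- **That baseline is ignored.** The ANCOVA must carry some covariate and may well carry baseline; the word that opens "additional adjustment for imbalanced baseline factors" hints that some adjustment is already in place. The primary outcome also divides by baseline volume, and binary progression is defined against the participant's own baseline grade. Only the t-test and chi-squared test clearly lack covariate adjustment.
- **That both continuous tests are assigned to the same endpoint.** The sentence covers continuous outcomes as a class. What is missing is which test decides the primary outcome.
- **That data-driven covariates contaminate the main result.** The imbalance rule is confined to optional supplementary analyses.
- **That scanner differences show site predicts outcome.** Each knee is scanned on the same unit at both times, one reader measures the pair, and the outcome is within-person change. The differences make a site effect plausible; they do not establish one.
- **That false positives are inflated or the trial is underpowered.** The calculations above show neither.

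**Conclusion.** The point holds as a modest, free improvement. The stratification factor is absent from every stated between-arm analysis, the choice between t-test and ANCOVA for the primary outcome is open, the ANCOVA covariates are unnamed, and three promised adjustments have no place in any model.

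The size is limited. Primary power moves from about 79.5 % to 81–84 % if site and baseline together explain 5–10 % of the variance, and hardly at all if they explain 2 %. Since the primary outcome is already scaled by baseline volume, the share due to baseline may be small. The 8–20 % excess in the WOMAC standard error applies only if the t-test is chosen over the listed ANCOVA. Both R² and the correlation are assumptions. The unsettled choice of primary test and covariates is at least as serious as the lost precision, because it can be removed only before the data are seen.

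**What to change.** - **Primary outcome:** one linear model of annual percentage change in tibial cartilage volume on arm, site and baseline cartilage volume.
- **WOMAC:** ANCOVA on arm, site and baseline score.
- **Binary progression of defects and BMLs:** logistic regression on arm, site and baseline grade. The odds ratio from this model is conditional on the covariates, so report a standardised risk difference beside it.
- **Sensitivity analyses:** keep the t-test and chi-squared test here.
- **Other covariates:** replace the imbalance trigger with a short prespecified list chosen for prognostic value.
- **Promised adjustments:** reconcile the bone area, medication and smoking sections with that list, stating for each whether it enters a model and which one. Use baseline values only; Table 2 already schedules medication and smoking at month 0.

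The cost is wording. Site, baseline volume, baseline grades and baseline WOMAC are already collected, and the sample size need not change. Covariates in the analysis model should also enter the multiple-imputation model.

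### Subgroups that respond better are to be found by stratified analyses alone, which do not test whether the treatment effect differs between strata

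*Protocol article*

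**What the plan says.** The last sentence of the Statistical analysis section sets both the aim and the method: "Pre-specified analyses to identify subgroups which may respond better to treatment will be examined using stratified analyses". It goes on: "variables include radiographic OA and co-pathology present on MRI". The list is open, and no cut-points, number of strata or stratum sizes are given.

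The article contains no treatment-by-subgroup interaction, no heterogeneity test, no multiplicity rule for subgroups and no statement that these analyses are exploratory. The same section mentions linear and logistic regression only as supplementary adjustment for baseline imbalance, not as a way to compare effects between subgroups.

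**The concern.** To say that one subgroup responds better is to say that its treatment effect is larger than that of the remaining patients. That is a statement about a difference between two effects. Stratified analyses supply the two effects separately, with no test of the difference.

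Readers commonly fill the gap by comparing p-values: significant in one stratum, not significant in the other, therefore a responder group. Each stratum holds only part of a sample sized for the overall comparison, so such a split pattern arises easily by chance when the effect is the same in everyone. At stake is a claim that atorvastatin works only in a certain radiographic or MRI phenotype. Calling the analyses pre-specified would lend that claim weight.

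**Working it through.** **Inputs from the Sample size calculation (Primary outcome) and Randomisation sections**
- Control rate and SD: "the rate of tibial cartilage volume loss in the control group was 3.0 +/− 3.0 per annum", read as % per year.
- Effect and alpha: "in the intervention group (2.0 %) compared with the control group (3.0 %), with alpha error 0.05, two-sided significance", that is, a difference of 1.0 % per year.
- Evaluable number and power: "With 140 participants in each arm, we will have 80 % power to detect a 30 % reduction in the rate of cartilage volume loss". The same difference is called 33 % earlier in that paragraph, and a true 30 % would be 0.9 % per year.
- Allocation is 1:1. The expected maximum dropout is 20 %, and 140 / 0.80 = 175 per arm, 350 in total, as stated.

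**Inputs that the article does not give (assumptions):** two strata per variable, their relative sizes, and the same true effect and SD in both strata.

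**Step 1: reproduce the plan's power.** SE = 3.0 × √(2/140) = 0.359. Power = Φ(1.0/0.359 − 1.96) = Φ(0.83) = 0.796. This agrees with the stated 80 % (0.794 with the noncentral t).

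**Step 2: power inside each stratum.**
- Equal strata, 70 per arm each: SE = 3.0 × √(2/70) = 0.507; power = Φ(1.972 − 1.96) = 0.505 (0.499 with the noncentral t).
- 30:70 split, 42 and 98 per arm: SE = 0.655 and 0.429; power = 0.333 and 0.646.

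**Step 3: chance that exactly one stratum is significant**, P = pA(1 − pB) + pB(1 − pA).
- Equal strata: 2 × 0.505 × 0.495 = 0.500. A simulation of 20,000 trials gave 0.499.
- 30:70 split: 0.646 × 0.667 + 0.333 × 0.354 = 0.549.

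**Step 4: vary the assumptions** (140 per arm unless stated; ranges run from a 50:50 to a 90:10 split).

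| Uniform true effect (% per year) | P(exactly one stratum significant) |
|---|---|
| 1.0 | 50 % to 68 % |
| 0.9 | 49 % to 62 % |
| 0.5 | 28 % to 30 % |
| 0 | 9.5 % (4.9 % counting only results in favour of treatment) |
| 1.0, with all 175 per arm | 48 % to 73 % |

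**Step 5: the interaction test.**
- Its false-positive rate under a uniform effect was 5.0 % in the same simulation.
- With 70 per arm per stratum its SE is √(0.507² + 0.507²) = 0.717. Power is Φ(1.0/0.717 − 1.96) = 0.29 for a true between-stratum difference of 1.0 % per year, and 0.80 for a difference of 2.0.
- With two subgroup variables, assumed independent and each split equally, at least one false signal arises in 66 % of trials by comparing significance at the planned effect, and in 9.6 % by interaction tests.

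**The case against.** The strongest reply is that the article never says how stratum results will be turned into a subgroup claim. Stratified estimates are compatible with a formal heterogeneity test, and showing them is good practice. The article is condensed, and an analysis plan that is not shown may contain the interaction term. This stands in part. A reader might infer that the protocol commits to declaring a differential response whenever one stratum is significant and the other is not, and hence that false claims will follow. The text does not state that rule, so the 50 % is the error rate of one use that the wording leaves open. What remains is that the article does name a method for a stated comparative aim, and the named method does not answer it.

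Two further readings are tempting and are not supported.
- A reader might infer that the risk is as large in a null trial. With no effect in either stratum, one-stratum-only significance occurs 9.5 % of the time, and 4.9 % in favour of treatment, which is close to the error rate of an interaction test.
- A reader might infer that MRI co-pathology could be taken from the month-24 scan, so that subgroups depend on what happened after randomisation. Nothing in the article indicates this. Table 2 schedules the X-ray at screening only, and progression of cartilage defects and bone marrow lesions is handled separately as an outcome. The unstated word baseline is an ellipsis in a condensed text.

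**Conclusion.** The point holds as a mismatch between aim and method: the sentence seeks subgroups with a better response and names only analyses that do not compare strata. The size is conditional. About 50 % (equal strata) or 55 % (30:70) requires three things: comparison of strata by significance, two strata per variable, and a uniform effect near the planned 1.0 % per year. At half that effect it is 28 to 30 %.

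The primary and secondary comparisons, the sample size and the conduct of the trial are not affected. The change is worth making because it is cheap and the possible misreading is serious, but it does not threaten the main conclusion.

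**What to change.** Replace the sentence with wording along these lines: *For each named subgroup variable, a treatment-by-subgroup interaction will be tested in the primary model. Treatment effects within subgroups will be shown with 95 % confidence intervals for description. These analyses are exploratory.* For a continuous endpoint this means a linear model with treatment, subgroup and their product; for a binary endpoint, the corresponding logistic model.

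Optionally, add that MRI co-pathology is read from the baseline scan. That is a clarification, not the correction of an error.

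The cost is a change of analysis wording, with no new data and no change to sample size. The downside is the low power of the interaction test: about 29 % for a 1.0 % per year difference between equal strata. Few subgroup claims will be possible, and a non-significant interaction must not be read as proof that the effect is uniform.
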